**Objective:**

The objective of this study is to adapt the scoring system as a tablet app (potentially scalable approach) to assess feasibility of use and to validate whether the scoring system accurately predicts prematurity by itself, over and above birth weight in a large sample of newborns.

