## Introduction

An estimated 15 million children per year (11% of live births) are born prematurely (less than 37 weeks of gestation), predominantly in Africa and Asia [1]. Prematurity rates are increasing globally and of concern because prematurity is a well-recognized risk factor for increased neonatal mortality and morbidity [2-4]. In settings where the incidence and adverse consequences of prematurity are the highest (ie, resource-limited settings), pregnant women may not know the date of their last menstrual period (LMP) and ultrasound is often not available—particularly first-trimester ultrasound, when estimates of gestational age (GA) are more accurate [5]. Since premature birth may not be anticipated by health care providers prior to labor and delivery [6,7], it is important that prematurity be identified at birth so that preterm neonates receive effective interventions as soon as possible after delivery [8].

When prenatal GA is unavailable, it can be estimated at birth by physical examination of the newborn using scoring systems such as the 12-item New Ballard Score (NBS) [9] and the 22-item Dubowitz score (DWS) [10]. A simplified 11-item scoring system adapted from the NBS was developed by Meharban Singh in 1975 and is in use in India [11]. However, even the use of simplified GA scoring systems in first (Primary Health Centers) and second (district and regional healthcare centers) level facilities in resource-limited settings, where the majority of the world’s neonates are born, is difficult. Further, predicted GA from these scores has often been compared with women’s reports of their LMP, and is not a reliable gold standard, such as first trimester ultrasound [12]. In addition, these scoring systems have not been adequately evaluated for regional, geographical, racial or ethnic robustness. A pragmatic postnatal GA assessment tool that can be used by community birth attendants or auxiliary nurse midwives (ANMs) who deliver the majority of newborns in rural health settings is urgently needed to optimize referral and care of preterm neonates when prenatal GA is unavailable.

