### Eligibility Criteria for the Newborns

During 12-hour study shifts, all mothers who meet the inclusion criteria and have no exclusion criteria (Textbox 1) will be informed about the study and invited to participate. Exclusion criteria were determined on the basis of conditions that could interfere with the assessment of the neonate’s posture. Mothers who are willing to participate will complete a consent process and sign the consent form.

Since it is frequently not possible to obtain and confirm the estimated GA by ultrasound, we decided *a priori* to have additional exclusion criteria for analysis eligibility, to improve the likely validity of the GA estimated by ultrasound, as follows:

Women whose estimated GA from the date of the LMP is not within 1 week of the GA estimated from the ultrasound;Neonates with GA at birth <20 weeks or >44 weeks based on either the date of the LMP or ultrasound;Two independent assessments of the newborn were not available within the first 24 hours of life; andANMs who had not assessed at least 100 newborns during the study were unavailable.

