#### Analysis plan

Firstly, we will use the Fleiss kappa statistic to estimate agreement between GA (as a dichotomous outcome) measured by ANM-1 and ANM-2. Since our goal is to evaluate the use of the T-SGAS by ANMs, we will not determine which AMN is “correct” (eg, by having a third AMN independently assess the GA of the baby to resolve disagreement). Instead, we will assess the screening accuracy (sensitivity, specificity, prevalence of preterm) of the T-SGAS for both ANMs using 4 different reference standards: LMP alone, ultrasound alone, either LMP or ultrasound, and both LMP and ultrasound (when GA by ultrasound is within 1 week of the GA estimated by the date of the LMP) [19]. We will also determine the predictive accuracy using the area under a receiver operator curve, based on predicted probability estimates obtained from logistic regression. We will determine from the data the optimal cutoff for the dichotomization of the T-SGAS using tree analysis. For this analysis, each of the four aforementioned reference standards will be separately considered as dependent variables and the birth weight and the T-SGAS as independent variables.

Secondly, we will use latent class analyses [20-23] to predict a preterm birth when neither the GA based on the date of the LMP nor GA based on the ultrasound are treated as a reference standard. Finally, we will conduct classification and regression tree (CART) analyses to identify specific items from the T-SGAS and combine them with birth weight to achieve an improved prediction of a preterm birth, since birth weights are universally measured in health facilities soon after birth. The CART analyses will also provide an optimum protocol for implementation of the T-SGAS in community settings, since birth weights are now universally measured in the health facilities soon after birth. Improvement in discrimination and reclassification using the T-SGAS over the traditional method that uses birth weight and LMP will be quantified using the integrated discrimination improvement index and the net reclassification index, respectively [24,25].

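### The IDI/NRI comparator includes LMP, which defines or closely tracks every reference standard for preterm birth, so these indices cannot show what T-SGAS adds to birth weight

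*Protocol article*

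**What the plan says.** The Analysis plan section assesses screening accuracy against "4 different reference standards: LMP alone, ultrasound alone, either LMP or ultrasound, and both LMP and ultrasound". For the AUC and cutoff analysis it specifies that "each of the four aforementioned reference standards will be separately considered as dependent variables and the birth weight and the T-SGAS as independent variables"; LMP is not a predictor there. The section's last sentence then introduces a different comparator: "Improvement in discrimination and reclassification using the T-SGAS over the traditional method that uses birth weight and LMP will be quantified". IDI is to serve for discrimination and NRI for reclassification. That sentence names no outcome.

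Three other places bear on it:

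- Eligibility Criteria for the Newborns excludes from analysis "Women whose estimated GA from the date of the LMP is not within 1 week of the GA estimated from the ultrasound".
- The Objective in the Abstract asks whether the score "accurately predicts prematurity by itself, over and above birth weight in a large sample of newborns". LMP is not mentioned.
- The Introduction describes the intended setting as one where "pregnant women may not know the date of their last menstrual period (LMP) and ultrasound is often not available".

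**The concern.** IDI and NRI measure how far a new marker improves a baseline model's separation of cases from non-cases. They are informative only if the baseline predictors are distinct from the definition of a case. Here LMP-based gestational age sits on both sides: it is in the comparator, and it is all or part of the outcome in three of the four standards. In the fourth it is held within 1 week of the outcome by the rule on who is analysed.

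IDI and NRI are also the only indices that the plan names to quantify improvement over an existing method. Run as written, they could be reported as evidence that T-SGAS adds almost nothing, even if it adds materially to birth weight. Birth weight is what the objective asks about, and it is what a midwife has at hand when LMP is unknown.

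**Working it through.** **Plan's own figures.** The article gives no IDI or NRI value to reproduce. Its sample sizes do reproduce approximately and are not affected. With n = (1.96√(p0q0) + 0.8416√(p1q1))² / (p1 − p0)², sensitivity 0.60 against 0.65 gives 742 preterm, and 742/0.10 = 7420 (stated 7440). Specificity 0.70 against 0.75 gives 638 term, and 638/0.90 = 709 (stated 704).

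**Definitions.** Let p_old and p_new be the predicted risks without and with T-SGAS.

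- IDI = (mean p_new − mean p_old among preterm) − (mean p_new − mean p_old among term).
- NRI = [P(up) − P(down) among preterm] + [P(down) − P(up) among term].

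**LMP alone (no assumption needed).** LMP-based age below 37 weeks is the outcome. The baseline gives p_old = 1 for every preterm and 0 for every term newborn, with AUC 1.000. Adding T-SGAS leaves p_new = p_old, so IDI = (1 − 1) − (0 − 0) = 0. Nobody can move up from 1 or down from 0, so NRI = 0. A logistic fit would show complete separation and have no finite maximum-likelihood estimate.

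**The other three, under the 1-week rule (arithmetic only).** Let L and U be gestational age at birth by LMP and by ultrasound, with |L − U| ≤ 1. If L < 36 then U < 37; if L ≥ 38 then U ≥ 37. Reading *either* as preterm by at least one method and *both* as preterm by each, L leaves the outcome undetermined only here:

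- ultrasound alone: 36 ≤ L < 38;
- either: 37 ≤ L < 38;
- both: 36 ≤ L < 37.

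T-SGAS can add information only inside those narrow bands.

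**Size, by simulation.** The inputs below are assumptions; the documents give none except the preterm prevalence of about 10%.

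- Simulation A: 200,000 newborns; gestational age about N(39, 1.55) plus an early tail; LMP error SD 0.5 week in 80% and 2.5 weeks in 20%; 25% early ultrasound, the rest late and size-related; 1-week rule applied.
- Simulation B: N = 7440, 8 replicates per setting; about 10% preterm; dating-error SD 0.7 to 1.5 weeks; correlation with gestational age 0.5 to 0.7 for T-SGAS and 0.55 for birth weight; LMP entered as weeks or as below 37 yes/no; run with and without the 1-week rule.

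IDI for adding T-SGAS:

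| Reference standard | A: over birth weight | A: over birth weight + LMP | B: over birth weight + LMP, rule applied | B: same, rule not applied |
|---|---|---|---|---|
| LMP alone | 0.048 | 0.0000 | 0 | 0 |
| Ultrasound alone | 0.043 | 0.0004 | 0.001–0.019 | 0.006–0.061 |
| Either | 0.046 | 0.0002 | 0.0005–0.008 | 0.003–0.022 |
| Both | 0.048 | 0.0001 | 0.001–0.011 | 0.004–0.060 |

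In B with the rule applied, IDI over birth weight alone was about 0.06 to 0.20 and NRI about 0.07 to 0.20. With LMP in the baseline, NRI was −0.002 to 0.016.

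**Share of the increment kept.** In A: 0.0004/0.043 = 0.9%, 0.0002/0.046 = 0.4% and 0.0001/0.048 = 0.2%. In B with the rule: at most about 11%. The loss is therefore roughly 89% to over 99%.

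In B without the rule, ultrasound alone keeps between 0.0064/0.0867 = 7% (error SD 0.7, T-SGAS correlation 0.5, LMP in weeks) and 0.061/0.1075 = 57% (error SD 1.5, T-SGAS correlation 0.7, LMP dichotomised).

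**T-SGAS replacing LMP.** Comparing birth weight + T-SGAS with birth weight + LMP gives IDI of about −0.27 to −0.81 in B with the rule applied. Against LMP alone, any reclassification away from a perfect baseline can only be for the worse.

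**The case against.** **The sentence names no outcome.** This stands. The four standards are made dependent variables in the preceding paragraph, for the AUC and cutoff analysis. The IDI/NRI sentence closes a paragraph that opens with latent class analysis, in which neither LMP nor ultrasound serves as the reference. But the text does not link IDI/NRI to the latent classes, and the only observed preterm outcomes in the plan are the four standards. The missing outcome needs to be stated; it does not remove the overlap.

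**A reader might infer that the result is zero by construction throughout.** The documents support that only for LMP alone. Ultrasound is a separate measurement, and its near-zero result depends on the 1-week rule. The Abstract and the eligibility section apply that rule to the analysis set, whereas the Analysis plan attaches it only to the *both* standard. Without it, the increment against ultrasound alone is attenuated but not near zero.

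**A reader might infer that at least 99% of the increment always disappears.** That figure comes from one assumed scenario; other plausible settings leave up to about 11% even with the rule.

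**A reader might infer that the objective is answered wrongly.** That goes too far. The AUC/tree analysis and CART use birth weight and T-SGAS without LMP, so the objective is partly served elsewhere. With LMP alone, separation would also tend to show itself as a failed fit rather than pass as a credible null.

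**An LMP-containing baseline can be legitimate.** This also stands. Whether T-SGAS improves on birth weight and LMP, judged against ultrasound, is a fair question, and the Conclusions make ultrasound the comparator for the key outcome. LMP need not be removed from every model.

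**Conclusion.** The point holds and the sentence is wrong as written; it should be fixed. Against LMP alone, IDI and NRI for adding T-SGAS are exactly 0, and this needs no assumption. Against the other three standards in the concordant sample, roughly 89% to over 99% of the increment over birth weight is lost. That range rests on assumed dating errors, correlations and coding of LMP, and the loss is smaller if the 1-week rule is not applied.

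If T-SGAS is to replace LMP, IDI in the concordant sample is strongly negative. Without the 1-week rule, the replacement IDI against ultrasound alone ran from about −0.29 to +0.03, so the strong negative there depends on the rule as well. With the rule applied, neither reading measures what T-SGAS adds to birth weight.

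The kappa, sensitivity and specificity, AUC/tree, latent class and CART analyses and the sample size are untouched.

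**What to change.** Reword the last sentence of the Analysis plan so that IDI and NRI compare birth weight with birth weight plus T-SGAS, and name the reference standard or standards used as outcome.

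If a baseline with LMP is kept, label it secondary. Judge it only against ultrasound alone, ideally in the first-trimester subset already foreseen in the Discussion (Principal Findings), without selecting on LMP-ultrasound agreement. Do not use it where LMP defines any part of the outcome.

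The main change costs one sentence, with no new data and no change to the sample size. The optional secondary analysis needs the records of women excluded for LMP-ultrasound disagreement; the data collector already enters both dates on form SGAS03 before analysis eligibility is decided.

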## Results

The results of the T-SGAS development process will be as follows: (1) successful development of the Android app with iterative improvements based on feedback from end users; (2) successful training of ANMs, who are the main skilled birth attendants in Primary Health Centers and District and Regional level hospitals in India; and (3) successful implementation of the quality control procedures. Enrollment began on July 27, 2015 and ended on March 28, 2016. Results are anticipated in June 2019.

## Discussion

### Principal Findings

The T-SGAS and its evaluation by the research protocol has the potential to provide a new way for neonates born at first level care facilities and of unknown GA to be promptly referred to second or tertiary level care facilities, if the baby is preterm. Access to optimal care for preterm babies has the potential to improve outcomes in this at-risk population. An anticipated strength of the development of the app is the iterative development process based on user feedback. An anticipated strength of the evaluation is the large sample size of neonates that will be studied and the future analysis of the ability of ANMs to accurately assess GA using the app. If effective, the T-SGAS has the potential for rapid scale-up and the app could easily be modified to efficiently transfer medical data to referral facilities.

An important anticipated limitation of this study is that most fetal ultrasounds in India are obtained in the third trimester, instead of the ideal timing in the first trimester, in part to reduce the risk of the abortion of female fetuses. Whenever a first trimester ultrasound is done, we will obtain that report for GA dating and plan to conduct a subgroup analysis on the subset of pregnancies for which a first trimester ultrasound is available, providing there are sufficient first trimester ultrasound studies. We also recognize that prospectively collected data on the LMP or recall of the LMP earlier in pregnancy, as well as a first trimester ultrasound, could all improve the accuracy of the GA assessment. Conversely, the inability to accurately recall the LMP can impact study enrollment and is considered to be a further limitation of this study. However, the accuracy of all ultrasounds will likely be improved by requiring the GA by ultrasound being within 1 week of the mothers’ assessment of GA, based on her LMP.

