### Analysis

#### Sample Size

We have assumed that the prevalence of preterm births will be approximately 10% in this population. In a 2-sided test for sensitivity, a sample size of 7440 will achieve 80% power at a significance level of 0.05 when the sensitivity under the null hypothesis is 0.60 and the sensitivity under the alternative hypothesis is 0.65. This sample size will also be sufficient to achieve 80% power at a 0.05 significance level in a 2-sided test for specificity, when the specificity under the null hypothesis is 0.70 and the specificity under the alternative hypothesis is 0.75, which requires a minimum of 704 subjects.

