### Conclusions

This paper describes the development of the T-SGAS and the research protocol to evaluate its use by ANMs in 3 second (District and Regional) level hospitals in Nagpur, India. Key outcomes will include whether the ANMs can correctly identify preterm babies using the app, compared to GA assessments by ultrasound obtained during pregnancy. This approach has the potential to improve outcomes in preterm infants born in first (Primary Care Centers) level facilities where their GA at birth may not be known if ANMs can accurately use the T-SGAS to assess GA and promptly refer those babies that are born prematurely.

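### Late-scan dating error is likely shared with birth weight, so the ultrasound-based standards can understate what T-SGAS adds to birth weight, and the 1-week LMP rule only partly corrects this

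*Protocol article*

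**What the plan says.** The Abstract's Objective is to "validate whether the scoring system accurately predicts prematurity by itself, over and above birth weight in a large sample of newborns". The Abstract's Background frames the problem as telling preterm from low birth weight babies.

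The Analysis plan names four reference standards: LMP alone, ultrasound alone, either, and both. For the tree analysis, "each of the four aforementioned reference standards will be separately considered as dependent variables and the birth weight and the T-SGAS as independent variables". It adds latent class analysis with neither LMP nor ultrasound as the reference, CART combining T-SGAS items with birth weight, and the IDI and NRI for T-SGAS over a traditional method based on birth weight and LMP.

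The Conclusions describe the key outcome as correct identification of preterm babies "compared to GA assessments by ultrasound obtained during pregnancy". In Principal Findings the article expects that "most fetal ultrasounds in India are obtained in the third trimester, instead of the ideal timing in the first trimester", and plans a first-trimester subgroup if there are enough such scans.

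The section on eligibility criteria for the newborns excludes from analysis women whose LMP and ultrasound gestational ages (GA) are not within 1 week of each other. Quality Control Procedures and Principal Findings both say that this rule will likely improve ultrasound accuracy. The Analysis plan, in contrast, mentions the 1-week condition only when it defines the combined standard.

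**The concern.** The article treats late scanning as a loss of precision. For the birth-weight question it is also likely to be a bias with a direction. If a late scan infers GA from fetal size, a small term fetus is dated too young and is then born light. The reference calls the baby preterm, birth weight agrees, and a T-SGAS that correctly says term is scored as wrong. The reference error is shared with one predictor and not, or much less, with the other.

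At stake is the added-value half of the objective, in the babies for whom the score was developed: the Introduction says that it was built for low birth weight newborns. The 1-week rule is offered as the remedy, so it matters whether the rule removes the shared error.

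**Working it through.** **The plan's own figures.** The only computed figures are the sample sizes: "a sample size of 7440 will achieve 80% power at a significance level of 0.05" (sensitivity 0.60 against 0.65), and 704 for specificity 0.70 against 0.75. The one-sample formula is n = [1.96·√(p0·q0) + 0.8416·√(p1·q1)]² / (p1 − p0)².
- Sensitivity: (0.960 + 0.401)² / 0.0025 gives 742 preterm babies; 742 / 0.10 = 7420.
- Specificity: (0.898 + 0.364)² / 0.0025 gives 638 term babies; 638 / 0.90 = 709.

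Both agree closely with the article. They concern the accuracy of T-SGAS by itself and do not change with this point. The article gives no figure for added value, so its sensitivity to shared error has to be simulated.

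**Assumed inputs, none of them in the article except the roughly 10% prevalence.**
- GA: 88% N(39.2, 1.2) and 12% N(36.3, 2.4) weeks, which puts 10.3% below 37 weeks.
- Birth weight: mean 2800 + 130·(GA − 39) g, coefficient of variation 13%. Let z be standardised size for GA.
- T-SGAS: GA plus error with SD 1.8 weeks, independent of z.
- LMP: GA plus error with SD 1 week, independent of z.
- Late ultrasound: GA + 1.5·[ρ·z + √(1 − ρ²)·noise] weeks.

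The gain is the AUC of a logistic model with birth weight and T-SGAS, minus the AUC of birth weight alone, for reference GA below 37 weeks. Against true GA it is 0.094 (birth weight alone 0.83, T-SGAS alone 0.90).

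| Standard | ρ = 0 | ρ = 0.3 | ρ = 0.5 | ρ = 0.7 |
|---|---|---|---|---|
| Ultrasound, no 1-week rule | 0.073 | 0.041 | 0.027 | 0.018 |
| Ultrasound, 1-week rule | 0.088 | 0.067 | 0.051 | 0.034 |
| LMP, 1-week rule | about 0.088 | 0.073 | 0.057 | 0.041 |
| LMP, no 1-week rule | 0.086 | 0.086 | 0.086 | 0.086 |

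Relative to 0.088, the filtered losses are:
- ultrasound: 1 − 0.067/0.088 = 24%, 1 − 0.051/0.088 = 42%, 1 − 0.034/0.088 = 61%;
- LMP: 17%, 35% and 53% by the same arithmetic.

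A repeat run gave values within about 0.004 of these.

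**Why the rule carries the bias into LMP.** It keeps a baby only if the ultrasound error and the LMP error differ by at most 1 week. Among those kept, the two errors resemble each other, so LMP error takes on the size component of the ultrasound error.

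**A second set of assumptions** (size SD 330 g, LMP error SD 0.7 to 1.5 weeks, ρ = 0.4, 0.6, 0.8):
- Filtered ultrasound gain: 0.046-0.061, 0.029-0.043, 0.016-0.023.
- Filtered LMP gain: 0.048-0.070, 0.033-0.054, 0.020-0.034.
- Unfiltered LMP gain: 0.063-0.088 at every ρ.
- A first-trimester-like scan (error SD 0.4 weeks, ρ = 0): about 0.092.
- Correlation of LMP error with size after filtering: 0.16 to 0.60, from zero before.
- SD of z among babies kept, from 1 before: 0.86-0.91 at ρ = 0.6 and 0.73-0.84 at ρ = 0.8. The rule preferentially drops babies whose size departs from their dates.

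**The IDI and NRI.** Their comparator already contains LMP. An LMP-alone outcome would then be predicted partly by itself, and the either and both standards also contain LMP. The only listed outcome without LMP is ultrasound alone, which is the standard most exposed to late-scan error.

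**The case against.** A reader might infer that the birth-weight question is judged only against late ultrasound, with the optional first-trimester subgroup as the sole safeguard. The documents do not support that. LMP alone is one of the four standards, latent class analysis uses neither dating method as the reference, and the 1-week rule excludes discordant babies. The Conclusions' ultrasound comparison concerns identifying preterm babies; it does not make ultrasound the outcome for added value.

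A reader might also take the unfiltered ultrasound losses, from 1 − 0.041/0.073 = 44% to 1 − 0.018/0.073 = 75%, as the size of the problem. They do not describe an analysis set restricted by the 1-week rule, where the losses are smaller.

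It is also fair that every decisive input is assumed, including the independence of T-SGAS error from size, which was not varied. The statement on scan timing describes India in general. The study takes the earliest scan, and the trimester mix among enrolled women is not given. The article does disclose late scanning as an important limitation. The Introduction calls LMP reports an unreliable gold standard, so making LMP the single primary standard would be a trade-off, not a correction.

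What does not stand is that the listed safeguards settle the matter. If the 1-week rule covers all analyses, the LMP standard inherits part of the bias. Latent class analysis is assigned to predicting preterm birth, not to the gain over birth weight. The first-trimester subgroup has no stated threshold and no stated role in the birth-weight comparison.

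**Conclusion.** The point holds as likely attenuation, not as complete masking: the gain shrank whenever the ultrasound error was correlated with size, but never reached zero. For correlations of 0.3 to 0.7, the filtered AUC gain falls from about 0.09 to 0.07-0.03 on ultrasound and to 0.07-0.04 on LMP, against about 0.086 on LMP without the filter. These are illustrative ranges, not estimates for this study. They rest on late scans dating by fetal size, on the assumed error SDs, and on T-SGAS error being unrelated to size.

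How far LMP alone protects the comparison depends on a contradiction in the article. If the eligibility section governs, LMP is filtered and partly biased. If the Analysis plan's narrower wording governs, LMP alone is unfiltered and largely free of the problem. The change is worth making because it concerns a stated objective and needs only analysis wording.

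**What to change.** Amend the Analysis plan as follows.

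1. For every analysis that compares or combines T-SGAS with birth weight, also report results on LMP alone without the 1-week exclusion, and on first-trimester ultrasound. Split the ultrasound-standard results by trimester of the earliest scan, and label the late-scan results as likely to favour birth weight.
2. For the IDI and NRI, do not use an outcome based on LMP while LMP is in the baseline model. Report the first-trimester ultrasound outcome next to ultrasound alone.
3. Report T-SGAS sensitivity and specificity within birth weight <2500 g and ≥2500 g, which answers the preterm-versus-low-birth-weight question directly.
4. Reconcile the eligibility section (1-week rule for all analyses) with the Analysis plan (rule attached only to the combined standard).

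Enrollment has ended, so only the analysis can change. Form SGAS03 already holds LMP dating, dating by the earliest ultrasound, and birth weight, and it is completed before analysis eligibility is decided. The planned first-trimester subgroup implies that scan timing is available. The cost is a few more tables, LMP recall error in the unfiltered analysis, and wider intervals in the first-trimester subset.
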